**Evaluation of curative effect on angina pectoris symptoms**	
Significant effect	Disappearance of symptoms or almost disappearance of angina pectoris symptom efficacy index ≥70%.
Effective	The frequency, degree and duration of pain attacks were significantly reduced by 30% ≤ angina pectoris symptom index <70%.
Invalid	The symptoms are the same as those before treatment. 0 ≤angina pectoris symptom efficacy index <30%.
Aggravate	The frequency, degree and duration of pain attacks were aggravated, the score of angina pectoris was increased, and the curative effect index of angina pectoris symptoms was <0.

Description: angina symptom efficacy index = (pre-trial angina symptom score-post-trial angina symptom score)/pre-trial angina symptom score × 100%. The symptom score of angina pectoris is the sum of the scores in Table 2. Total effective rate = (significant effect + effective)/sample size × 100%.

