#### Inclusion criteria

The inclusion criteria are as follows:

(1) Meet the SAP diagnostic criteria,(2) Age between 60 and 80 years old,(3) Classified as I–III based on severity, according to the Canadian Cardiovascular Society (CSS) grading of angina pectoris,(4) Sign the informed consent form.

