**Angina pectoris symptom scoring standard**			
**Number of seizures**		**Symptom**	**Integral**
	None	No attack within a week	0 point
	Mild	Attack 2–6 times a week	2 point
	Moderate	Attack 1–3 times a week	4 point
	Severe	Attacks more than 4 times a week	6 point
The degree of pain	None	No attack within a week	0 point
	Mild	Heavier than daily activities of physical activity caused angina pectoris	2 point
	Moderate	Daily physical activities cause angina pectoris, and daily activities are restricted.	4 point
	Severe	Physical activities that are lighter than daily activities cause angina pectoris, and daily activities are obviously limited.	6 point
The duration of the pain	None	No attack within a week	0 point
	Mild	The pain lasts ≤5 min	2 point
	Moderate	5 min < The pain lasts <10 min	4 point
	Severe	The pain lasts ≥10 min	6 point
Dosage of nitroglycerin	None	None	0 point
	Mild	Take 1–4 tablets a week	2 point
	Moderate	Take 5–9 tablets a week	4 point
	Severe	Take more than 10 tablets a week	6 point
		Total	____point

**Table 3 T3:** Evaluation of curative effect on angina pectoris symptoms.

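### Patients with attacks who enter at 6 or 8 points on the primary symptom score can respond only by becoming attack-free, and from 8 to 24 points a one-band improvement never counts as response

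*Protocol article*

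**What the plan says.** The article defines the primary outcome in Tables 2 and 3 under Primary outcome. "The symptom score of angina pectoris is the sum of the scores in Table 2", and each of the four items (attack frequency, degree of pain, duration of pain, nitroglycerin use) takes 0, 2, 4 or 6 points. For frequency, degree and duration, 0 points requires "No attack within a week". The lowest non-zero entries for these items carry 2 points: "Attack 2–6 times a week", "Heavier than daily activities of physical activity caused angina pectoris" and "The pain lasts ≤5 min". Nitroglycerin scores 0 when none is taken, whether or not attacks continue.

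Table 3 uses the percentage fall from the pre-trial score. An index of at least 30% is *Effective* and at least 70% is *Significant effect*; the total effective rate pools the two. The grade below reads "The symptoms are the same as those before treatment. 0 ≤angina pectoris symptom efficacy index <30" (per cent).

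The Inclusion criteria require "Classified as I–III based on severity" and set no minimum Table 2 score or attack frequency. Under Secondary outcome, item (2), a patient who stops nitroglycerin is graded *Significant effect*. The Statistical analysis section compares categorical data by chi-square or Fisher's exact test and continuous data by t or Mann-Whitney test, without reference to the baseline score.

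**The concern.** One percentage cut is applied to a coarse score that has a floor while attacks persist. Near that floor the 30% threshold cannot be met by partial improvement. The responder definition then becomes freedom from attacks for the mildest eligible patients with attacks, and at least a two-band fall for everyone else with attacks. A reader of the total effective rate would take it as the proportion who improved by 30%, and would take *Invalid* as unchanged. At stake are the meaning of the headline rate, its sensitivity to partial benefit near the floor, and its exposure to chance imbalance in baseline score when the test ignores that score.

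**Working it through.** **Inputs.** Item scores, the index formula and the 30% and 70% cuts come from Tables 2 and 3. The entry range comes from the Inclusion criteria.

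**The plan's own figure.** The formula under Sample size, with p = (0.762 + 0.458)/2 = 0.61, gives n = (1.960 + 1.282)² × 2 × 0.61 × 0.39 / 0.304² = 54.1, rounded up to 55. Then 55/0.80 = 68.75, or 69 per group, as stated. This point does not change that figure or the later increase to 90 per group.

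**Step 1, the floor.** With at least one attack in the scored week, frequency, degree and duration each score at least 2, and nitroglycerin can be 0. The minimum total is 2 + 2 + 2 + 0 = 6.

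**Step 2, what is reachable.** Index = (entry − post)/entry × 100%. The best index with attacks continuing uses post = 6. A one-band fall is 2 points. The smallest qualifying fall is 30% of the entry score, rounded up to a multiple of 2.

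| Entry score (attacks present) | Best index, attacks continuing | Index for a one-band fall | Points needed for 30% |
|---|---|---|---|
| 6 | 0% | none possible with attacks | 2 |
| 8 | 25% | 25% | 4 |
| 10 | 40% | 20% | 4 |
| 12 | 50% | 16.7% | 4 |
| 14 | 57.1% | 14.3% | 6 |
| 16 | 62.5% | 12.5% | 6 |
| 18 | 66.7% | 11.1% | 6 |
| 20 | 70% | 10% | 6 |
| 22 | 72.7% | 9.1% | 8 |
| 24 | 75% | 8.3% | 8 |

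At 6 and 8 the best index with attacks continuing is below 30%. From 10 it is above. The 70% grade is out of reach with attacks continuing unless the entry score is at least 20.

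**Step 3, examples at entry 8** (order: frequency, degree, duration, nitroglycerin).
- (2,2,4,0) to (2,2,2,0): attacks shorten from, say, 8 to 3 minutes. Index 2/8 = 25%, *Invalid*.
- (2,2,2,2) to (2,2,2,0): 4 tablets a week become none. Index 25%, *Invalid*. Secondary outcome item (2) grades the same change *Significant effect*.

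**Step 4, edge cases.**
- An entry of 6 made up of nitroglycerin alone, (0,0,0,6), is already attack-free. That patient can respond by using less (6 to 4 = 33.3%). An entry of 8 always includes attacks.
- Becoming attack-free is necessary from 6 or 8 with attacks, but not always sufficient: 8 to (0,0,0,6) is still 25%.
- The printed frequency bands overlap: mild is "Attack 2–6 times a week" and moderate is "Attack 1–3 times a week". As printed, one attack a week scores 4, which makes that patient's floor 4 + 2 + 2 = 8. This is a separate defect, and correcting it would not lower the floor of 6.

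**The case against.** The strongest reply is that this is a coarse scale with a percentage cut, not a fault peculiar to mild patients. A one-band fall fails from 10 as well, with a lower index (20%) than from 8 (25%), and entries of 8, 10 and 12 all need 4 points. This stands. What remains specific to 6 and 8 is that no partial improvement at all can qualify while attacks continue.

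A reader might infer a loss of power. The documents do not support one. They do not give the share entering at 6 or 8. The class I limit bears only on the degree item, and training during hospitalization may point to patients with more symptoms. The direction is also open: patients with few attacks may reach an attack-free week more easily, and that scores 100% if no nitroglycerin is used. The planning rates of 76.2% and 45.8% come from an earlier study whose scale is not shown, so they may already contain the same floor.

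A reader might also infer that partial benefit goes unrecorded. It does not. Secondary outcome item (1) collects attack duration, weekly frequency and nitroglycerin dose at every visit, and the Statistical analysis section provides between-group tests. Nor is the type I error at risk, since randomization protects it.

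Finally, stratification and adjustment are often left to an analysis plan. But Tables 2 and 3 are complete definitions, and the article itself names the unadjusted tests. The proposal improves on what is stated.

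**Conclusion.** The point holds as a matter of arithmetic. Among patients with attacks at entry, those at 6 or 8 points cannot reach 30% while any attack remains in the scored week (best 0% and 25%). From 10 they can, by a fall of at least two bands. A one-band fall is *Invalid* at every entry score from 8 to 24, yet Table 3 calls it unchanged, and for nitroglycerin stopped from the lowest band the article's own secondary outcome gives the top grade. The total effective rate therefore does not mean the same thing at every baseline. The enumeration needs no assumption beyond reading Table 2 per scored week. How many patients are affected is unknown, so neither a shift in the response rates nor a loss of power can be put in figures. The consequence is for interpretation and sensitivity, not for the validity of the test.

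**What to change.** Keep Tables 2 and 3 as the responder definition and make three changes before unblinding.

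(a) Replace the unadjusted chi-square test of the total effective rate by a Mantel-Haenszel analysis stratified by baseline symptom score (6–8 against 10 or more), and report response in each stratum. State where patients who are attack-free at entry are placed, since some score below 6.

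(b) Adjust the planned between-arm comparisons of weekly attacks, attack duration and nitroglycerin use for their baseline values, and name them as the companion to the responder rate.

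(c) State that patients with attacks who enter at 6–8 can respond only by becoming attack-free in the scored week, which is necessary but not always sufficient. Reword the *Invalid* description so that an index from 0 to below 30% is not called unchanged.

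The cost is some wording and a few extra tables, from data already collected. No visits or patients are added. The small downside is that the headline rate carries a qualification.

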#### Primary outcome

The main outcome index is the total effective rate of angina pectoris symptoms, described in detail in Tables 2, 3. Data will be collected at baseline, weeks 4 and 8, and months 3 and 6 after enrollment.

**Table 2 T2:** Angina pectoris symptom scoring standard.

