#### Secondary outcome

(1) Clinical symptoms: after confirming that the patients meet the inclusion criteria, researchers will ask about and record the clinical symptoms of the patients (including the duration of angina pectoris, frequency of weekly attacks, and the dosage of nitroglycerin) at baseline, weeks 4 and 8, and months 3 and 6 after enrollment.(2) Stopping rate of nitroglycerin: This will be recorded at the baseline and at weeks 4 and 8 and months 3 and 6 after enrollment.① Significant effect: discontinuation of nitroglycerin after treatment;② Effective: the dosage of nitroglycerin after treatment is >50% less than that before treatment;③ Ineffective: after treatment, the dosage of nitroglycerin decreased by <50% or increased, compared with that before treatment.(3) SAQ: This is a 19-item self-administered questionnaire measuring five dimensions of coronary artery disease: physical limitation (question 1), anginal stability (question 2), anginal frequency (question 3–4), treatment satisfaction (question 5–8), and disease perception (question 9–11) (28). The 19 items will be scored individually to obtain the total SAQ score, which is transformed into a standard score according to this formula: Standard score = (actual score – lowest score of the dimension) x100/(highest score of the dimension – lowest score of the dimension). Patients' quality of life and body function are proportional to the score, which will be recorded at the baseline and weeks 4 and 8 and months 3 and 6 after enrollment.(4) SF-36: The MOS item short will be used from the health survey (SF-36) to assess patients' quality of life. As a concise health questionnaire, SF-36 comprehensively summarizes the quality of life of the subjects from eight aspects: Physical Functioning (PF), Role-Physical (PR), Bodily Pain (BP), General Health (GH), Vitality (VT), Social Functioning (SF), Role-Emotional (RE), and Mental Health (MH). There are 36 questions, and the quality of life is proportional to the score (29). SF-36 is effective in detecting the health perception of the general population, easy to use, and highly accepted by patients, and studies have proven it to be a promising tool due to its high reliability (30, 31). SF-36 will be recorded at baseline, weeks 4 and 8, and months 3 and 6.

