**Efficacy criteria of electrocardiogram**	
Significant effect	ECG returns to roughly normal or normal range of electrocardiogram.
Effective	After treatment, the ST segment rises ≥0.05 mv, but does not reach the normal level, the main lead causes the T waves to become shallow >25%, or the T wave changes from flat to upright; severe arrhythmia is improved.
Invalid	ECG is roughly the same as before.
Aggravation	The ST segment decreased more than 0.05 mV after treatment. In the main ECG leads, T wave changes more deeply (up to 25%); or T wave changes from upright to flat, or upright T wave inversion, ectopic rhythm, atrioventricular or ventricular block.

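### The primary efficacy index divides by a baseline score that can be 0 for an eligible patient, who then cannot respond but still counts in the denominator

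*Protocol article*

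**What the plan says.** The protocol article fixes the primary endpoint in full. Under Primary outcome: "The main outcome index is the total effective rate of angina pectoris symptoms, described in detail in Tables 2, 3". The note below Table 3 gives the index, "angina symptom efficacy index = (pre-trial angina symptom score-post-trial angina symptom score)/pre-trial angina symptom score × 100", and adds: "The symptom score of angina pectoris is the sum of the scores in Table 2". A patient is *effective* at an index from 30% to below 70%, and shows a *significant effect* at 70% or more. The rate is then "Total effective rate = (significant effect + effective)/sample size × 100".

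In Table 2, attack number, pain degree and pain duration each score 0 for the same condition, "No attack within a week". The nitroglycerin item scores 0 when none is taken.

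On severity, the inclusion criteria ask only for a grade: "Classified as I–III based on severity". The other criteria are the diagnosis, age 60 to 80 and consent. Neither the inclusion nor the exclusion criteria set a minimum attack count, nitroglycerin use or symptom score.

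Among the secondary outcomes, the nitroglycerin stopping rate calls a patient effective if "the dosage of nitroglycerin after treatment is >50% less than that before treatment", and ineffective if the fall is under 50% or the dose rises.

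**The concern.** The endpoint rule does not cover the population that the eligibility criteria admit. A patient with stable angina who has one quiet, tablet-free week at baseline enters with a score of 0. The printed formula then gives no value, and a score already at its floor cannot fall by 30%. Because the denominator is the sample size and not the number of patients with a computable index, that patient is a non-responder whatever the exercise does.

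At stake is sensitivity. Patients who cannot respond shrink both arms' rates by the same factor, so the difference shrinks too. The nitroglycerin rate has a smaller version of the problem: someone who takes none at baseline can neither stop nor halve it.

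**Working it through.** **1. Can the score be 0?** Yes. Four items, each scored 0, 2, 4 or 6, are summed, so the range is 0 to 24. No attack in the week gives 0 + 0 + 0, and no tablets adds 0.

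**2. What does the index give at baseline 0?** (0 − post)/0. With post = 0 this is 0/0; with post > 0 it is a negative number over 0. It is undefined for every later score. The next possible baseline score is 2, where the index works (2 to 0 gives 100%), so 0 is the only failing value.

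**3. The plan's own sample size.** Inputs from the Sample size section: 76.2% versus 45.8%, two-sided α = 0.05, power 90%, 20% dropout. With mean rate 0.61 and (1.960 + 1.2816)² = 10.507:

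n = 10.507 × 2 × 0.61 × 0.39 / 0.304² = 54.1, so 55; 55/0.80 = 68.75, so 69 per group.

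This matches the stated 69, which the article then raises to 90. The point here does not touch that calculation.

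**4. Effect of patients scoring 0.** Assumptions: a share f in each arm scores 0 at baseline (not in the article, so shown as a range), and 76.2% and 45.8% apply to patients with a computable index. Evaluable patients per arm: 90 with full retention, or 90 × 0.80 = 72 after the planned dropout.

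- Whole-sample denominator, as written: rates become 0.762(1 − f) and 0.458(1 − f), with n unchanged.
- Denominator restricted to baseline score above 0: rates unchanged, n becomes n(1 − f).

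Power = Φ[(d − 1.96 × SE0)/SE1], where d is the difference, SE0 = √(2p̄(1 − p̄)/n) and SE1 = √((p1(1 − p1) + p2(1 − p2))/n).

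Example, f = 20%, n = 72, as written: p1 = 0.6096, p2 = 0.3664, d = 0.2432, SE0 = 0.0833, SE1 = 0.0808; (0.2432 − 0.1633)/0.0808 = 0.989; power 0.839.

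Same f, restricted: n = 57.6, d = 0.304, SE0 = 0.0909, SE1 = 0.0864; (0.304 − 0.1781)/0.0864 = 1.457; power 0.927.

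| f | Rates as written | Difference (points) | Power as written, 72 / 90 per arm | Power restricted, 72 / 90 per arm |
|---|---|---|---|---|
| 0% | 76.2% v 45.8% | 30.4 | 97% / 99% | 97% / 99% |
| 10% | 68.6% v 41.2% | 27.4 | 92% / 96% | 95% / 98% |
| 20% | 61.0% v 36.6% | 24.3 | 84% / 91% | 93% / 97% |
| 30% | 53.3% v 32.1% | 21.3 | 74% / 83% | 89% / 95% |

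**5. Nitroglycerin boundary.** Effective needs a fall of more than 50%; ineffective is a fall of less than 50% or a rise. A fall of exactly 50%, such as 2 to 1 or 4 to 2 tablets, has no class.

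**The case against.** **The share is unknown and may be small.** This stands. Nothing in the article supports a particular f, and references to exercise during hospitalisation suggest that many participants are inpatients. The increase to 90 per group also absorbs a good deal: the 90% target holds to about f = 20% with full retention and to about f = 10% after 20% dropout.

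**The planning rates may already include the dilution.** The article gives 76.2% and 45.8% simply as effective rates from a previous drug study. If that study also used a whole-sample denominator, applying (1 − f) counts the loss twice. This too stands, and is why the figures are conditional.

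**The wording of Table 3 supplies a class without the index.** A patient at 0 throughout has unchanged symptoms (*invalid*), and one who moves from 0 upwards has a raised score (*aggravate*). That is a fair reading, but neither class is a response, so it confirms the consequence.

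**This is detail for the analysis plan.** Only in part. The article prints the formula, cut-offs and denominator itself, and the printed rule fails for patients whom it admits.

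Two stronger readings are tempting. One is that patients scoring 0 bias the comparison through chance imbalance between arms. Randomisation balances them in expectation, the test's ordinary error rate covers chance imbalance, and the statistical analysts are to be blinded; what remains is dilution towards no difference. The other is that the ECG outcome shares the flaw, since its top class reads "ECG returns to roughly normal or normal range of electrocardiogram" and a normal tracing cannot return to normal. Table 4 has no division and states no whole-sample denominator, and an unchanged ECG has its own class. That is a ceiling effect and is not part of this point.

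**Conclusion.** The point holds as a defect in the primary endpoint's definition: for an eligible patient with baseline score 0 the index is undefined, no response is reachable, and the patient stays in the denominator. That much follows from the text alone.

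The size does not. It rests on an assumed f, equal in both arms, and on the planning rates applying to scorable patients. Under those assumptions the loss against the restricted denominator at 72 per arm is about 3, 9 and 15 percentage points of power for f of 10%, 20% and 30%; at 90 per arm it is about 2, 6 and 12. A reader might infer that the trial is underpowered. The documents do not show that, because f is not given and 90 per arm leaves a margin.

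The unclassified 50% fall in nitroglycerin is real but minor.

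**What to change.** - State that the symptom score is recorded before the allocation envelope is opened. The outcome text places it before the experiment, but Table 1 first marks the total effective rate in the allocation column. Researchers open the envelopes and are not blinded, so restricting on the score is free of selection only if scoring comes first.
- Define the total effective rate among randomised patients with baseline score above 0.
- Report by arm the number scoring 0 and their later scores, so that patients who worsen from 0 are not lost from view.
- Add, as a sensitivity analysis, a comparison of the symptom score itself, adjusted for baseline, in all randomised patients. It needs no division.
- For the nitroglycerin stopping rate, restrict to users at baseline and assign a fall of exactly 50% to one class.

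The cost is a few lines of text, a slightly smaller denominator, and a primary result that applies to patients with symptoms at baseline. Recruitment has started, so the rule should be fixed before outcome data are examined.

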### Sample size

The sample size was calculated according to the effective rate of the Baduanjin group and the control group. Referring to the previous research (27), it is assumed that the effective rate of the combination of traditional Chinese medicine and western medicine is 76.2%, and the effective rate of western medicine is 45.8%. Based on the class I error rate of α = 0.05 and the efficacy of 90% (II error rate of β = 0.1), bilateral test, and considering the shedding of 20%, the experiment was expanded to 69 people. Because the reference study is drug intervention, considering that this study is non-drug intervention, we continue to expand the sample size to 90 people in each group, a total of 180 people.

$$\begin{array}{l} n=\frac{{\left(u_{\alpha }+u_{\beta }\right)}^{2}\left(1+1/k\right)p\left(1-p\right)}{{\left(p_{e-}p_{c}\right)}^{2}} \end{array}$$

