### Statistical analysis

A full-analysis set (FAS), per-protocol analysis set (PPS), and safety analysis set (SAS) will be created according to the principle of intentional therapy (34). FAS participants are identified as those who received at least one exercise. Those who adhere to the treatment plan but changed groups midway are part of the PPS. For safety indicator assessment, researchers will use the SAS to analyze the incidence of adverse events and laboratory indicators. Statistical analysis will be conducted by third-party statisticians blinded to experimental grouping and intervention methods, using SPSS 25. We will analyze the baseline demographic data to determine the comparability between the two groups. Mean ± standard deviation will be used for continuous variables that conform to normal distribution, and median and quartile methods will be used for continuous variables that do not conform to normal distribution. The Chi-square test or Fisher's exact test will be used to compare classified counting data. The paired *t*-test will be used to compare differences within the group, and the independent-sample *t*-test will be used to compare differences between groups. If the data do not conform to normal distribution, a Wilcoxon paired test and Mann-Whitney U test will be used to analyze intra- or inter-group differences. *P* < 0.05 is considered as statistically significant.

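### The order of the four Table 3 symptom grades and the four Table 4 ECG grades goes unused; keep the effective rate as primary and add an ordinal analysis beside it

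*Protocol article*

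**What the plan says.** All references are to the protocol article.

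- **Score (Tables 2 and 3).** Four items are each scored 0, 2, 4 or 6. "The symptom score of angina pectoris is the sum of the scores in Table 2", so the total runs from 0 to 24.
- **Grades (Table 3).** The percentage fall in that score places each patient in one of four ordered classes, with cuts at 70%, 30% and 0. The top class is defined as "Disappearance of symptoms or almost disappearance of angina pectoris symptom efficacy index ≥70"%; below it come *effective*, *invalid* and *aggravate*.
- **Primary outcome (Table 3 footnote).** "Total effective rate = (significant effect + effective)/sample size × 100"%.
- **Sample size.** The calculation compares two proportions: "the effective rate of the combination of traditional Chinese medicine and western medicine is 76.2"% against "the effective rate of western medicine is 45.8"%. The size per arm is then raised: "Because the reference study is drug intervention, considering that this study is non-drug intervention, we continue to expand the sample size to 90 people". No smaller effect is stated.
- **ECG (Table 4).** A secondary outcome with four ordered classes of its own; the *invalid* class reads "ECG is roughly the same as before".
- **Statistical analysis.** "The Chi-square test or Fisher's exact test will be used to compare classified counting data". The Mann-Whitney test is named only for data that are not normally distributed. No test that uses order is assigned to graded outcomes.

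**The concern.** In the primary rate, a patient whose angina disappears counts the same as one with a 30% reduction, and a patient who gets worse counts the same as one with a 29% reduction. Two arms could share one effective rate while differing in complete relief or in worsening, and the primary result would not show it.

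For the ECG grades, the only categorical method given ignores order when applied to a 4×2 table: a move from *invalid* to *significant effect* is treated as no further than a move to the neighbouring class.

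What is at stake is some efficiency and some information about the direction of change. Efficiency matters more if Baduanjin's advantage is smaller than the one borrowed from the drug study. That is plausible, because the controls also exercise 3–5 times a week for 8 weeks.

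**Working it through.** **1. The plan's own figure.** Inputs from Sample size: 76.2%, 45.8%, two-sided α = 0.05, power 90%, 20% dropout. The mean rate is (0.762 + 0.458)/2 = 0.61.

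n = (1.960 + 1.282)² × 2 × 0.61 × 0.39 / 0.304² = 54.1, so 55; 55/0.8 = 68.75, so 69 per group. This matches the stated 69. After the increase to 90, a 20% loss leaves 90 × 0.8 = 72 evaluable per arm.

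**2. Binary power at the planned effect.** Power = Φ[(0.304 − 1.96 × SE₀)/SE₁], with SE₀ = √(0.4758/n) and SE₁ = √(0.4296/n). Here 0.4758 = 2 × 0.61 × 0.39 and 0.4296 = 0.762 × 0.238 + 0.458 × 0.542.

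- n = 72: (0.304 − 0.1593)/0.0772 = 1.87, power 96.9%.
- n = 90: (0.304 − 0.1425)/0.0691 = 2.34, power 99.0%.

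**3. Loss at the planned effect.** The article gives no split of patients among the grades, so any figure for an ordinal test needs assumptions. Under proportional odds, taking 10–50% of control responders as *significant effect* and 5–30% of control non-responders as *aggravate*, simulated power of the rank test on four grades is:

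- n = 72: 98.3–99.2%, a gain of 1.4–2.3 points.
- n = 90: 99.5–99.8%, a gain of 0.5–0.8 points.

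Even a comparison of the full score, taken as normal, reaches only 99.8% at n = 72, a gain of 2.9 points. The loss is thus about 0.5–3 points.

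**4. Smaller effects (assumed, not in the plan).** Solving the plan's formula for 72 evaluable per arm, 90% power corresponds to 72.4% versus 45.8%, and 80% power to 68.9% versus 45.8%. Effects in this region were simulated with a normal underlying improvement shifted equally across all grades. At the planned effect that shift is probit(0.762) − probit(0.458) = 0.818 SD. Among controls, 10–30% were *significant effect* and 5–15% *aggravate*. Results at 72 per arm:

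| Baduanjin rate (control 45.8%) | Binary test | Rank test, four grades |
|---|---|---|
| 65.8% | 69–70% | 76–81% |
| 68.7% | 80–82% | 87–90% |
| 72.0% | 90% | 95–97% |
| 76.2% (planned) | 97% | 99% |

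Across the three smaller effects the rank test gains about 4–12 points over the binary test. An unordered 4×2 chi-square does no better than the binary test (76–79% at 68.7%), so the rank test gains about 7–16 points over it.

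The size depends on the assumed split. Under proportional odds with the wider splits of step 3, the gain over the binary test at 72 per arm is 2–5 points at 72.4%, 3–7 at 69.0% and 3–8 at 66.6%.

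**5. When the gain reverses.** Suppose benefit moves patients only from *invalid* to *effective*, leaving the outer grades unchanged. At 68.7% versus 45.8% and 72 per arm, the binary test has 81% power and the rank test 28–60%. At 70% versus 45.8% and 90 per arm, with 25% of control responders *significant effect* and 20% of control non-responders *aggravate*, the figures are 91% and 65%.

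**The case against.** A responder rate is a legitimate and readily understood primary endpoint, and here the sample size is built on it. The trial is registered and recruitment has begun, so a new primary test would be a mid-trial change that no longer matches the calculation. The increase from 69 to 90 is the plan's own protection against a weaker effect. Step 5 shows that the rank test can lose far more than it gains. All of this stands, and it defeats any call to replace the primary test.

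Graded information is also partly kept: attack frequency, duration, nitroglycerin dose and the SAQ are secondary outcomes. This stands in part. The pain-degree item, the total score and the distribution of grades are not listed as outcomes.

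The article is condensed, and a supportive ordinal analysis may be in an analysis plan that is not shown. Nor does it say that the ECG grades will be compared as a 4×2 table. Both are fair. The point rests only on the rule the article does fix for categorical data, which takes no account of order. For the same reason, the lack of a cited source for the 30% cut is not held against the plan.

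A reader might infer that dichotomising costs a large share of power at effects the plan was designed for. The documents do not support that: they state one effect, and there the loss is at most about 3 points. The larger figures belong to effects inferred from an increase in size that was never quantified.

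**Conclusion.** The point holds as a modest one about efficiency and information. The primary rate merges worsening with reductions below 30%, and the stated categorical methods ignore the order of both graded outcomes.

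At the planned effect binary power is already 97–99%, so the primary test is neither wrong nor underpowered on that account. A gain of about 4–12 points over the binary test, or about 7–16 over an unordered chi-square, needs two assumptions that the documents do not supply: a true effect near 66–72% versus 45.8%, and benefit spread across all grades. If the second fails, the gain becomes a loss.

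The power figures were worked out for the Table 3 grades. The article gives no expected ECG effect, so for Table 4 only the direction of the argument carries over, under the same condition.

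**What to change.** 1. Keep the total effective rate and its two-proportion test as primary, to match the Sample size section.
2. Pre-specify, as the first supportive analysis of the primary outcome, a Mann-Whitney or proportional-odds comparison of the four Table 3 grades. Choose one before analysis starts. Report a common odds ratio with its confidence interval, and show the grade distribution by arm so that complete relief and worsening are visible.
3. Use the same ordinal test, in place of an unordered chi-square, for the four ECG grades in Table 4.
4. Before either step, reconcile the attack-frequency bands in Table 2. Mild covers 2–6 attacks a week, moderate 1–3 and severe more than 4, so two or three attacks fit both mild and moderate, and five or six fit both mild and severe. The binary endpoint needs this just as much.

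Cost: a little extra analysis, with no added patients, visits or data. Mann-Whitney is already among the named methods. The drawbacks are an effect measure less familiar than a response rate, and a gain that depends on benefit being spread across the grades.
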